### Secondary research questions

1. Can the above intervention reduce the proportion of people with single or recurrent falls (>1)?

2. Can the above intervention reduce fall-related injuries (including fractures)?

3. Can the above intervention reduce disability and improve quality of life?

4. Can the above intervention reduce institutionalisation and the need for the use of health services?

5. Is the intervention cost-effective and might it lead to overall cost-savings?

6. Can a screening questionnaire used in primary care reliably distinguish between low and high risk of falling?

7. Is there any difference in deaths between the two groups?

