#### Ascertainment of outcomes

The principal method will be self-reporting using the diary. This will contain a section on falls and the outcomes (carried on as usual, called for help, waited for someone to help, called GP, called ambulance, taken to hospital, nature of any injury). Additionally, there will be a section recording health service utilisation, covering primary care contacts and hospital admissions.

The self-reported data will be cross referenced where possible through access to GP records and hospital information systems. For hospital admissions, access to the case notes will be requested and the notes reviewed. This level of information will allow a more accurate ascertainment of events as well as the costs associated. Information on falls-related drug treatment (such as bone protection therapy) will be obtained from the GP records. These data will be collected by the project manager and project officer on standardised forms. The data collection will be subject to internal audit to ensure accurate and consistent data recording and avoid intraobserver and interobserver bias.

Institutionalisation data will be available from practice registers. Those who change practice as a result of changing address will be traced through the primary care trusts.

Disability and quality of life will be self reported by study participants. They will be asked to complete the Nottingham extended activities of daily living scale (NEADL)[24], Barthel index of Daily Living, EuroQol[25] and the falls efficacy scale[26]. These will be posted at the end of one year, along with reply paid envelopes. Non-responders will be sent a written reminder and if necessary a follow-up phone call ('hot pursuit').

EuoQol is included to facilitate cost-effectiveness and cost-utility calculations, but the Falls Efficacy Scale (FES) is a more sensitive measure of quality of life in this population, hence its inclusion[27]. The FES has been validated in the UK as both a face to face and self completed questionnaire[27]. The intraclass correlation coefficient is 0.58, suggesting fair agreement when used as a postal questionnaire. Both the Barthel index and the NEADL are well validated measures of functional ability and can be used as a postal questionnaire[24].

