### Data analysis

#### Power and sample size

With an expected rate of falls of 2/year per person[11], and an over dispersion parameter of 1.5 a clinically important risk reduction of 24% to 1.5 falls/year can be detected with 80% power and 5% significance (two-sided) in a trial of 160 participants in each arm giving a trial size of 320. This assumes a Poisson distribution with over dispersion. If the fall rate was 1/year per person[10] a risk reduction of 33% could be detected with this sample size (not a high risk population). To allow for an attrition rate of 20% (see below) we will recruit a total of 400 participants. To achieve this, 3125 subjects will need to be screened, of whom 40% may be at high risk of falls. Of these 1250, 20% are likely to be ineligible leaving 1000 potential participants of whom it is thought that 40% will agree to take part. This sample size will also have 80% power at the 5% significance level to detect a reduction of one third in the proportion of people with one or more falls, with an expected proportion with one or more falls of 50% at 12 months.

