#### Univariate and multivariate analyses

For the primary analysis, Poisson regression or if there is over-dispersion (likely), negative binomial regression will be used to estimate the incidence rate ratio comparing the rate of falls between the two randomised groups during the follow-up period. The number of falls will be the numerator and length of follow-up the denominator.

Secondary analysis will compare the following outcomes between treatment arms:

a) The proportion of people with one or more falls over the follow-up period, using logistic regression

b) Time to first fall using survival analysis

c) the proportion of people with injurious falls using logistic regression

d) the proportion of people institutionalised at 12 months using logistic regression

e) Impact on disability, quality of life, fear of falls, and use of health services will be assessed using linear regression models with transformations if necessary, although some of these comparisons will be underpowered.

f) Deaths will be compared between the two groups. The analysis will be survival analysis using Cox proportional hazards model.

All analyses will adjust for the strata used in the randomisation procedure. If there are other important baseline differences, for example in age or number of previous falls, multivariate analysis will be used to adjust for them.

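### The plan allows use of health services to be compared on a transformed scale, where the result need not agree with mean use, the quantity most relevant to its questions on service use and cost

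*Protocol article*

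**What the plan says.** Under Univariate and multivariate analyses, item (e) of the secondary analysis groups service use with disability, quality of life and fear of falls, and states that "use of health services will be assessed using linear regression models with transformations if necessary". No transformation and no criterion for using one is given. The same section plans Poisson or negative binomial regression for falls, with length of follow-up as the denominator.

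Two of the Secondary research questions depend on service use. Question 4 asks: "Can the above intervention reduce institutionalisation and the need for the use of health services". Question 5 asks: "Is the intervention cost-effective and might it lead to overall cost-savings". Ascertainment of outcomes describes the data: in the diary, "there will be a section recording health service utilisation, covering primary care contacts and hospital admissions". Economic analyses then values resource use at unit costs to form incremental cost-effectiveness ratios.

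**The concern.** Contacts and admissions per person are non-negative counts, usually with many low values, some zeros and a long right tail. Skew of that kind is the usual reason for transforming, so the conditional clause could well come into play.

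A regression on log(x+1) or square-root use tests whether the transformed means are equal. This coincides with equal mean use when the arms share a distribution shape, but not in general. This intervention could change the shape. The Treatment section describes medication review, referrals to opticians, chiropodists and other specialists, and follow-up therapy visits, all of which add small contacts. The trial also hopes to prevent injurious falls, and the Background attributes 49.4% of the cost of falls to inpatient admissions. A log scale gives more weight to the small contacts and compresses the heavy users, so changes that cancel in total use need not cancel after transformation.

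At stake is whether the answer to question 4 can be read alongside the answer to question 5. The test could report higher use in the intervention arm when mean use is equal, or miss a real fall in mean use that the costing shows.

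**Working it through.** **Step 1: the plan's own figure.** The sample size concerns falls only: "With an expected rate of falls of 2/year per person[11], and an over dispersion parameter of 1.5" and "a clinically important risk reduction of 24% to 1.5 falls/year", which "can be detected with 80% power and 5% significance (two-sided) in a trial of 160 participants in each arm". With variance equal to 1.5 times the mean,

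n per arm = (1.96 + 0.8416)² × 1.5 × (2 + 1.5) / (2 − 1.5)² = 7.849 × 5.25 / 0.25 ≈ 165,

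which is close to the stated 160. Allowing for 20% attrition, 320 / 0.8 = 400, as stated. No figure is given for service use, so 160 per arm and two-sided 5% are borrowed for the check below.

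**Step 2: assumptions, none of them from the protocol.** Use per person is negative binomial with mean m and size s:
- variance = m + m²/s
- share of non-users = (s/(s + m))^s

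Control has m = 6 and s = 1, so variance 42 and 1/7 ≈ 14% non-users. Follow-up is complete.

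**Step 3: formula.** On a scale f, let Δ be the difference between arms in the mean of f(x), with SE = √((V₁ + V₀)/160), where V is the variance of f(x) in each arm. The probability of rejection is about Φ(|Δ|/SE − 1.96) + Φ(−|Δ|/SE − 1.96). Means and variances of log(1+x) come from summing over the negative binomial probabilities.

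Example, equal means of 6, intervention s = 2: the mean of log(1+x) is 1.693 (SD 0.753) against 1.547 (SD 0.930) in control. Δ = 0.147, SE = √((0.567 + 0.865)/160) = 0.0946, Δ/SE = 1.55, rejection ≈ 34%.

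**Step 4: equal mean use (6 and 6), control s = 1.**

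| Intervention s | Variance | Non-users | Δ, log(1+x) | SE | Rejection, formula | Rejection, simulated |
|---|---|---|---|---|---|---|
| 1 (same shape) | 42 | 14% | 0 | 0.104 | 5% | 4.7% |
| 1.25 | 34.8 | 11% | 0.055 | 0.101 | 8% | 8% |
| 1.5 | 30 | 9% | 0.094 | 0.098 | 16% | 16–17% |
| 2 | 24 | 6% | 0.147 | 0.095 | 34% | 34–35% |
| 3 | 18 | 4% | 0.204 | 0.090 | 62% | 61–62% |

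The excess rejections almost all show the intervention arm as the higher user. The untransformed comparison has Δ = 0 throughout and rejects about 4% to 6% in simulation. The square root lies between the two: 7%, 12%, 21% and 39% for s = 1.25, 1.5, 2 and 3. Robust standard errors on the log scale do not help, because the quantity compared is what differs. If the intervention arm is instead more dispersed (s = 0.67 or 0.5), log(1+x) rejects 19% or 47%, now showing it as the lower user.

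**Step 5: a true 25% cut in mean use (6 to 4.5), control s = 1.**

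| Intervention s | Power on log(1+x) | Power untransformed |
|---|---|---|
| 1 (same dispersion) | Δ/SE = −0.210/0.101; 55% | Δ/SE = −1.5/0.646; 64% |
| 1.33 | 34% | 68% |
| 2 | Δ/SE = −0.086/0.094; 15% | Δ/SE = −1.5/0.595; 71% |

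Simulation gives 54% against 64%, 34% against 68%, and 13–15% against 72–74%.

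**Step 6: an illustration closer to the described mechanism.** Routine contacts average 4 in control and 5 in intervention. An admission component with mean 10 affects 20% and 10%. Mean use is equal: 4 + 0.2 × 10 = 6 and 5 + 0.1 × 10 = 6. Log(1+x) rejects 9.6%, untransformed 4.9%. For a true fall from 6 to 5 (4.5 + 0.05 × 10), power is 12% against 31%.

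**The case against.** - **The transformation is conditional.** The default in item (e) is untransformed linear regression, which holds its level in every case above. A reader might infer that the protocol commits itself to a transformed test. It does not: it permits one without naming it or saying when it applies. This stands.
- **Detail belongs to the analysis plan.** The choice of transformation and any back-transformation can be left there, and their absence is not the point. The point is that the article states a route which, if taken, compares a quantity other than mean use, although a method suited to counts is already planned for falls.
- **The mean is inferred.** No summary measure is named for question 4. The mean is the natural reading given the cost question and the costing, but it is a reading. Question 5 is answered by the economic analysis, where no transformation is mentioned. This stands, and nothing here suggests that the costing itself is at fault.
- **Pooling is inferred.** Nothing says that contacts and admissions are added into one total. Analysed separately, small contacts could not offset admissions within one outcome, although either count could still differ in shape between arms.
- **The large percentages need large shape changes.** A reader might infer that a false-positive rate of 34% to 62% is to be expected. The documents do not support that. Those cases more than halve the share of non-users while holding the mean exactly equal, and a test that rejects there is detecting a real difference in the pattern of use. The illustration in step 6 gives 9.6%.

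**Conclusion.** The point holds in a limited form. Item (e) permits a scale on which the comparison need not agree with mean use, for a secondary outcome where mean use is the most relevant quantity. With the same distribution shape in both arms the level stays at 5%, and the power loss for a 25% cut is modest, about 55% against 65%. If the intervention adds routine contacts while reducing heavy use, rejection at equal means can exceed 5%, by a little or a lot depending on the change in shape, and a true reduction can be missed.

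The sizes rest on assumed means and dispersions, on log(x+1) as the transformation, and on 160 per arm with complete follow-up. They are a range, not predictions for this trial. The article's remark that some comparisons in item (e) will be underpowered does not cover the point, since a larger sample would make rejection at equal means more frequent. This is a worthwhile, cheap improvement.

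**What to change.** In item (e), remove the option to transform for use of health services and state that mean use will be compared between arms, adjusted for centre, by one of two methods:
- the count model already planned for falls, with log link, follow-up time as the denominator and robust standard errors, giving a ratio of mean rates; or
- untransformed linear regression with robust or bootstrap standard errors, giving a difference in means.

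Keep any transformed analysis as a sensitivity analysis. In simulation the log-link model with robust errors rejected 5.0% to 5.3% at equal means, and its power was 75% for the 25% cut with s going from 1 to 2.

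The cost is one sentence, with no new data, participants or visits. The downside is some loss of precision for some distributions if the arms share the same skewed shape. In the equal-dispersion case above there was none.

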### Baseline measurements

Participating general practices will be asked to identify all patients aged 70 and over in their practice. Practices will be asked to exclude all those living in a nursing or residential home and those with terminal illness. The remaining subjects will be sent an invitation to participate by their general practice.

The invitation will include the patient information leaflet as well as a screening questionnaire which the subjects will be asked to return to the project officer. This screening questionnaire is based on published guidelines[1] and will be adapted for the local population in a pilot study. Those subjects not participating in the randomised study will be offered the opportunity to complete the monthly diaries only; data from these replies will be used to explore the predictive strengths of the screening questionnaire. The screening questionnaire will enable the identification of subjects deemed to be at high risk of falling and will include questions on previous falls history, mobility, use of walking aids and the number of medications. In addition to returning the questionnaire, subjects will be asked if they would be interested in participating in the study and if so to provide contact details, including phone number. The screening questionnaire will also ask about other exclusion criteria such as attendance at the day hospital. The replies will be analysed by the project officer and suitable participants for the study identified. Potential participants will be asked if they have had contact with either the day hospital or the primary care falls prevention service in the preceding year; in case of any doubt, verbal consent will be obtained to check their possible contact with these services with the day hospital or the primary care team.

A written invitation will be sent offering a home visit from the study nurse where no telephone contact is possible.

Those eligible subjects thought to be at high risk of future falls (approximately 1000) will then be sent a pack containing further information on the study, a falls prevention booklet ('Avoiding slips, trips and broken hips', Department of Health) and a consent pack.

The subjects will then be contacted by phone with the aim of:

• Clarifying any issues about the study

• Confirm responses to the screening questionnaire

• Invitation to take part

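### Adjustment of the primary analysis for age and previous falls depends on an undefined imbalance trigger instead of being fixed in advance

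*Protocol article*

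**What the plan says.** All references are to the Protocol article.

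- *Univariate and multivariate analyses* sets the primary comparison as an incidence rate ratio between randomised groups with length of follow-up as the denominator. On the model family it says: "Poisson regression or if there is over-dispersion (likely), negative binomial regression will be used to estimate the incidence rate ratio".
- The same section adjusts all analyses for the randomisation strata. *Randomisation* shows that these are centre only (Nottingham, Derby).
- It then adds: "If there are other important baseline differences, for example in age or number of previous falls, multivariate analysis will be used". Because this follows directly on a sentence about all analyses, it covers the primary one.
- Under *Baseline measurements*, the screening questionnaire "will include questions on previous falls history, mobility, use of walking aids and the number of medications". Falls history is therefore known before randomisation.
- *Subgroup analyses* already uses falls in the last year (0–1 against 2 or more) and age as factors.
- *Data monitoring and analysis* refers to a pre-specified analysis plan, which is not shown.

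**The concern.** Under randomisation, baseline differences between arms arise by chance. The sound reason to adjust a falls-rate comparison is that a covariate predicts falls, whether or not it happens to be unbalanced. The rule here looks at observed differences instead, and it leaves three things open:

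1. the threshold for an important difference;
2. the candidate covariates, since age and previous falls are only examples;
3. whether the adjusted estimate becomes the primary result or stands beside the centre-adjusted one.

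Two careful analysts could follow the text and report different primary rate ratios. When no imbalance is judged important, whatever precision falls history could provide is given up.

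**Working it through.** **1. The plan's own sample size.** The inputs, from *Power and sample size*, are "With an expected rate of falls of 2/year per person", "an over dispersion parameter of 1.5", "risk reduction of 24% to 1.5 falls/year" and "80% power and 5% significance (two-sided) in a trial of 160 participants in each arm". The section adds: "This assumes a Poisson distribution with over dispersion". I read 1.5 as the variance-to-mean ratio φ.

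- n per arm = (1.96 + 0.842)² × φ(λ₁ + λ₂)/(λ₁ − λ₂)² = 7.85 × 1.5 × 3.5/0.5² = 164.8.
- Power at 160 per arm: 0.5/√(1.5 × 3.5/160) = 2.760; 2.760 − 1.96 = 0.800; Φ(0.800) = 78.8%.
- On the square-root scale n is 164.0. With an exact 24% reduction (2 to 1.52), a log-scale formula with control-rate null variance gives 163.5. (2 to 1.5 is strictly 25%; this is immaterial here.)
- Attrition: 320/0.8 = 400.

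The stated 160 is reproduced to within rounding and choice of formula, with no covariate gain assumed. Reading 1.5 as a negative binomial dispersion would need 395 per arm, so that is not the reading used.

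**2. How often the trigger would fire.** Take 160 per arm and falls history split 50/50 (assumed). The standardised difference has SD √(2/160) = 0.112.

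- Trigger at p < 0.05: about 5% of trials.
- Trigger at a standardised difference above 0.1: P(|Z| > 0.1/0.112 = 0.894), about 37%.

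The protocol specifies neither. The undefined word therefore decides how often the primary model changes.

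**3. Precision at stake.** The documents give no prognostic strength for falls history. Assume a rate ratio of 1.5 to 3 for 2 or more against 0–1 prior falls, and 50% prevalence. The variance ratio (unadjusted to adjusted) from simulation is:

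| Assumed rate ratio | Variance ratio |
|---|---|
| 1.5 | 1.03–1.05 |
| 2 | 1.07–1.16 |
| 3 | 1.13–1.33 |

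Hand check of the top value, control arm, mean 2, residual dispersion k = 0.25, rate ratio 3 (group rates 1 and 3):

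- Unadjusted variance per person: 1/2 + 0.25 + 1.25 × (2/4)² = 1.0625.
- Adjusted information: 0.5 × (1/1.25 + 3/1.75) = 1.257, so the variance is 0.795.
- Ratio: 1.0625/0.795 = 1.34.

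With heavier residual dispersion the gain shrinks. At a rate ratio of 2 and k = 1.0 (200 per arm, variable follow-up), standard errors of 0.1321 and 0.1276 give (0.1321/0.1276)² = 1.07.

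**4. In power terms, on the protocol's inputs.** Power = Φ(2.760 × √VR − 1.96). Required n per arm is 165/VR, rounded up.

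| Variance ratio (VR) | Power at 160 per arm | n per arm for 80% |
|---|---|---|
| 1.00 | 78.8% | 165 |
| 1.05 | 80.7% | 158 |
| 1.15 | 84.1% | 144 |
| 1.25 | 87.0% | 132 |
| 1.33 | 88.9% | 125 |

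Simulated gains were about 1.5 to 7 points. The approximation reaches 88.9 − 78.8 = 10 points at the largest ratio, so the upper end is soft.

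**5. Error rate and movement of the estimate (simulation).**

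- Conditional adjustment under a fixed trigger: type I error 3.6–5.9%.
- Free choice between adjusted and unadjusted results: 5.9–8.2%, or 6.6–8.7% if age may also be added.
- Adjusted and unadjusted log rate ratios differ with an SD of 0.037–0.042 (95th percentile 0.07–0.08), against a standard error of 0.10–0.13. That is enough to move a borderline result.

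**The case against.** **The analysis plan may settle it.** The unseen plan could define an important difference or fix the covariates. Leaving that detail to it would be ordinary. But the protocol is not silent: it states a rule. A plan that follows the rule inherits the trigger, and a plan that fixes the covariates departs from it. The sentence needs changing either way.

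**Centre-only adjustment is valid.** This stands. Adding prognostic covariates improves efficiency and does not repair a bias. The sizing assumed no covariate gain, so it is unaffected.

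**The gain may be near zero.** This also stands. At a rate ratio of 1.5 it is 3–5% in variance, and recruiting only people screened as high risk may narrow the spread of falls history.

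Three stronger readings are tempting, and the documents do not support them:

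- *The whole primary model is left to the data, including the error distribution.* The rate ratio, the exposure and centre adjustment are all fixed. The Poisson or negative binomial choice is a declared rule with the likely branch named, and the sizing already assumes over-dispersion. At a true variance-to-mean ratio of about 1.6 or more, a likelihood-ratio test detected it in every simulated trial. The two models' log rate ratios differed with an SD of only 0.007–0.018.
- *Type I error is inflated.* That needs a free choice between results. The text does not plan one; it only fails to exclude it.
- *The trial has only about 50% power without adjustment.* Such figures arise if residual dispersion is set at 1.0. With 40% having 2 or more prior falls and a rate ratio of 2.5 to 3, that implies a variance-to-mean ratio of about 3.8–4.2 against the protocol's 1.5. They do not describe this trial as planned.

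**Conclusion.** The point holds for one sentence of the protocol. Adjustment of the primary analysis beyond centre rests on an undefined, open-ended judgement about observed imbalance. That is the wrong criterion for choosing covariates, and it leaves open whether the primary rate ratio is adjusted for falls history.

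The efficiency cost is modest and depends on assumptions: a variance ratio of about 1.03 to 1.33 if prior falls carry a rate ratio of 1.5 to 3 at 50% prevalence, with residual dispersion in the range simulated. The risk to the error rate, about 6–8% instead of 5%, exists only if the choice is made after seeing both results. The change is worth making because it removes an ambiguity in the primary estimate at almost no cost, not because the design is unsound.

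**What to change.** Replace the conditional sentence with a fixed primary model: the falls-rate regression already planned, with length of follow-up as exposure and with treatment arm, centre, number of falls in the previous year and age as covariates. State the form in which falls history and age enter. Label any further adjustment prompted by observed imbalance a sensitivity analysis that does not replace the primary result.

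Naming negative binomial regression outright would be a harmless tidy-up, but it is not required. The same covariates need not be imposed on secondary models where events may be few, such as deaths, institutionalisation and injurious falls; event numbers for these are not given.

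Make the change before any comparison of the arms. *Project milestones* lists an interim analysis and first-centre one-year results before the final analysis, without saying whether either compares arms.

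The cost is wording only. Falls history is asked at screening, both covariates are already needed for the planned subgroups, and the sample size stays as it is.
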